### **9.3 Multivariate analysis**

The effects of age, gender, body weight, blood pressure, medication, hemoglobin, lipids, quality-of-life, performance status and medication on the relation between each independent variable (demographic data, calcium-phosphate parameters, inflammation markers and calcification inhibitors), and primary outcomes will be determined with multivariate linear regression analysis. The effects of age, gender, body weight, blood pressure, medication, hemoglobin, lipids, quality-of-life, performance status and medication on the relationship between these independent variables and secondary outcomes (change in coronary calcifications score, change in pulse wave velocity) will be determined with multivariate linear regression analysis.

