### **Objective:**

1. To assess whether nocturnal hemodialysis and renal transplantation are associated with less progression of coronary arterial calcification, compared with conventional hemodialysis and peritoneal dialysis;
2. To identify risk factors for coronary arterial calcification in dialysis and transplant patients, and to assess a possible interaction with treatment modality.

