### **Secondary objectives:**

1. To assess whether frequent nocturnal hemodialysis and renal transplantation are associated with less progression of coronary artery stenoses, in comparison with conventional 3-times/week hemodialysis and with peritoneal dialysis;
2. To assess the association of calcium-homeostasis, in particular calcium, phosphate, PTH, and relevant medication, with the progression of coronary arterial calcifications and stenoses;
3. To assess the association of markers of inflammation, in particular CRP, interleukin-6, interleukin-1, von Willebrand factor, fibrinogen, with the progression of coronary arterial calcifications and stenoses;
4. To assess the association of calcification-inhibitors, in particular fetuin A, osteoprotegerin and matrix-Gla protein, with the progression of coronary arterial calcifications and stenoses.
5. To assess possible interaction of the abovementioned risk factors and the treatment modalities mentioned in the primary objective.

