## **9. STATISTICAL ANALYSIS**

### **9.1 Descriptive statistics**

The population characteristics are described with a categorical or continuous output, as appropriate.

The primary endpoint, coronary artery calcification score, is a continuous variable with a skewed distribution, and will be presented with its median and ranges. Progression of calcification score will be analyzed with multinomial logistic regression, dividing the coronary artery calcification score in three categories. The same goes for pulse wave velocity of the aorta and iliac arteries.

The calcification score of the different groups will be compared by regression analyses.

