### **9.2 Univariate analysis**

The relation between each independent variable (demographic data, calcium-phosphate parameters, inflammation markers and calcification inhibitors), and primary outcomes will be determined with univariate linear regression analysis. The relationship between these independent variables and secondary outcomes (change in coronary calcification score, change in pulse wave velocity) will be determined with univariate linear regression analysis. Because the relative change in calcification score can be independent from the initial absolute calcification score, the results will be corrected for initial calcification score.

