### **10.4 Benefits and risks assessment, group relatedness**

The potential value of this study lies in gaining insight in the process of artery calcification in patients with ESRD. With conventional dialysis methods, progression of arterial calcification occurs alarmingly fast. On theoretical grounds, it is plausible that progression is attenuated in patients with a renal transplant (low/normal phosphate, normal/high calcium) and patients on nocturnal hemodialysis (normal phosphate, normal calcium). However, no long-term data are available on this subject. Therefore it is difficult to advise dialysis patients about registration at the Eurotransplant Kidney Waiting List, especially for patients with advanced age, who have substantial perioperative morbidity and mortality.

The risk and burden to the patient are formed in this study by:

- calcium score MSCT: as described above (7.3 Study procedures) multislice CT is a very short procedure giving a low radiation dose (0.4-1.2 mSv);
- coronary MSCT: as described above (7.3 Study procedures) a coronary CT is also a very short procedure with a low radiation dose (3-4 mSv) (NB for comparison: a diagnostic abdominal CT scan delivers a dose of about 7-10 mSv);
- pulse-wave velocity: non-invasive measurement without risk;
- minor extra blood loss combined with routine venipuncture.

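### The marker regressions in 9.2 and 9.3 omit treatment modality, so on a pooled reading the associations are confounded by it, and the interaction objective has no matching analysis

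*Protocol*

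**What the plan says.** Secondary objectives 2 to 4 (section 2) ask whether calcium-phosphate parameters, inflammation markers and calcification inhibitors are associated with progression. Objective 5 adds "To assess possible interaction of the abovementioned risk factors and the treatment modalities mentioned in the primary objective", and objective 2 of the Summary likewise wants "to assess a possible interaction with treatment modality".

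The matching analyses are in section 9. Section 9.2 states: "The relation between each independent variable (demographic data, calcium-phosphate parameters, inflammation markers and calcification inhibitors), and primary outcomes will be determined" by univariate linear regression. Its only adjustment is that "the results will be corrected for initial calcification score". Section 9.3 gives the multivariate step with a named list: "The effects of age, gender, body weight, blood pressure, medication, hemoglobin, lipids, quality-of-life, performance status and medication on the relation" between each of those variables and the outcomes. Medication appears twice in that list; modality does not appear.

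Modality enters elsewhere, as a separate comparison. Section 9.1 says "The calcification score of the different groups will be compared by regression analyses", and section 4.4 says the effect of modality is analysed by linear regression. Section 4.4 then mentions a multivariate model for the risk factors without naming its terms.

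**The concern.** Modality is chosen by the patient and not randomised, and the protocol expects it to move both sides of these regressions. Section 10.4 finds it plausible that "progression is attenuated in patients with a renal transplant (low/normal phosphate, normal/high calcium) and patients on nocturnal hemodialysis", the latter with normal phosphate and calcium. Section 1 says that fetuin-A is low in end-stage renal disease and rises after transplantation. A variable that shifts both the marker and the outcome confounds their association if it is left out. Matching on age, sex, diabetes and dialysis duration (section 4.1) does not remove marker differences that the modality itself produces.

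What is at stake is how objectives 2 to 4 are read. If the primary hypothesis is true, a marker that merely differs between modalities can appear to be a risk factor, and the risk-factor results would partly repeat the modality comparison. Objective 5 is a stated aim for which the protocol specifies no model.

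**Working it through.** **1. The lists side by side.**
- 9.2 predictors: demographics, calcium-phosphate parameters, inflammation markers, inhibitors. Adjustment: initial score.
- 9.3 covariates: age, gender, weight, blood pressure, medication, hemoglobin, lipids, quality of life, performance status.
- Modality in either list: no. Interaction term anywhere in section 9 or in 4.4: no.

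**2. The plan's own figure.** Section 4.4 gives 22 patients per group for a 15% difference, mean 2370, two-sided alpha 0.05 and power 0.90. The difference is 0.15 × 2370 = 355.5. The printed formula with SD 352 gives 2 × (1.96 + 1.28)² × 352 / 355.5 = 20.8. A t-based calculation gives 21.6, so 22. The figure of 22 is reproduced and used below. The ratio 355.5 / 352 = 1.01 SD serves only as the upper of two assumed progression differences.

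**3. Set-up of the illustration.** There are four equal groups of n, so N = 4n. Marker and progression each have within-group SD 1. Nocturnal hemodialysis and transplantation differ from conventional hemodialysis and peritoneal dialysis by m SD on the marker and by y SD on progression. Within a modality the marker has no association with progression. The protocol gives no marker differences, so m and y are assumptions. The initial score and the 9.3 covariates are left out.

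Without modality in the model:
- expected slope b = (m·y/4) / (1 + m²/4)
- residual variance = 1 + y²/4 − b²(1 + m²/4)
- SE = √[residual variance / (N(1 + m²/4))]

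For n = 22, y = 1.01, m = 0.5: b = 0.126 / 1.0625 = 0.119; residual variance = 1.240; SE = √(1.240 / 93.5) = 0.115; b/SE = 1.03. The rejection rate at two-sided 0.05 is about 18%.

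For m = 1.0: b = 0.2525 / 1.25 = 0.202; residual variance = 1.204; SE = √(1.204 / 110) = 0.105; b/SE = 1.93. The rejection rate is about 49%.

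**4. Simulated rejection rates, modality omitted.**

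| n per group | y | m = 0.25 | m = 0.5 | m = 0.75 | m = 1.0 |
|---|---|---|---|---|---|
| 22 | 0.5 | 6% | 9% | 13% | 17% |
| 22 | 1.01 | 8% | 17% | 33% | 49% |
| 40 | 0.5 | 7% | 11% | 19% | 28% |
| 40 | 1.01 | 11% | 27% | 53% | 74% |

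With m = 0 the rate is about 5%. With modality as a four-level factor it is about 5% in every cell (4.5% to 6% across runs).

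**5. How much of the slope is between modalities.** The between-modality share of marker variance is (m²/4) / (1 + m²/4), which is 6% at m = 0.5 and 20% at m = 1.0.

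**6. The opposite case.** Let modality act on progression only through the marker, with slope 0.3 and 22 per group. The slope without modality is then unbiased (about 0.30). Its power is about 84% and 89% at m = 0.5 and 1.0, against about 80% with modality included.

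**7. Precision for objective 5.** For a contrast of slopes, two modalities against two, with SDs of 1, SE = √(2 / 2n) = 0.213 at n = 22. Power for slope differences of 0.3, 0.5 and 0.7 is about 29%, 65% and 91%. At n = 40 it is about 48%, 89% and 99%.

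**The case against.** The strongest reply has five parts.

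- **Pooling is not stated.** True. It is the natural reading, since no stratification is mentioned, but the confounding argument depends on it.
- **Section 9.2 is labelled univariate.** An unadjusted slope is what that label means, and 9.3 is the adjusted step. This stands, and it is why the change belongs in 9.3.
- **Calcium and phosphate may be mediators.** The protocol's rationale is that modality acts by correcting them. For such a marker the pooled slope is not biased and adjusting for modality costs some power (step 6). This stands for those markers. It does not help a marker that modality shifts without its lying on the path to calcification, and the unadjusted slope cannot tell the two apart.
- **The sizes are soft.** The 1.01 SD comes from the SD of a cross-sectional score and is not a stated contrast in progression. The marker shifts are assumed, and neither model was simulated with its listed adjustments. Medication in 9.3 includes immunosuppressants (section 7.3) and could stand in roughly for transplantation, though it does not clearly separate the three dialysis modalities. The figures therefore illustrate the mechanism and do not estimate the error of 9.2 or 9.3 as written.
- **An analysis plan may settle objective 5.** It may, so the claim is limited to what the protocol specifies. The covariate list is different: the protocol fixes it, and a plan that followed it would carry the omission forward.

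A reader might go further and infer that these models test modality differences instead of marker associations. Step 5 does not support that: the slope is a mixture, and mostly within-modality at moderate shifts. Objectives 2 to 4 also ask only for association, not for cause. Nor do the documents support an argument that a true calcium effect would be hidden because calcium is higher after transplantation. Section 10.4 gives no calcium level for conventional dialysis, and the Summary speaks of calcium being normalised by transplantation and nocturnal hemodialysis.

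**Conclusion.** The point holds in limited form. The predictor and covariate lists in 9.2 and 9.3 leave out treatment modality, and no modality-by-marker term is specified. If the cohorts are pooled, associations for markers that differ by modality are confounded, and objective 5 and Summary objective 2 have no matching analysis in the protocol. The second part does not depend on pooling or on any assumed effect size.

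The size of the first part depends on how far marker and progression both differ by modality. At 22 per group it ranges from no inflation (marker does not differ), through about 9% false positives (0.5 SD on both), to about 50% (1 SD on both), under the simplified model above. Secondary objectives are affected; the primary comparison between modalities is not. It should be corrected, and the correction is cheap.

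**What to change.** In 9.3, add treatment modality as a four-level factor to the regressions of outcome on each calcium-phosphate, inflammation or inhibitor variable, and state that the initial-score correction is kept. Take the modality-adjusted slope as the main answer to objectives 2 to 4, and keep the unadjusted 9.2 slopes as description. State that the cohorts are pooled, if that is the intention.

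For objective 5, name a short list of markers, add a modality-by-marker term for each, and report the slopes by modality with confidence intervals.

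The cost is a wording change and three degrees of freedom per model for the main effect, with no new data or patients. For markers through which modality acts, power falls by roughly 5 to 10 percentage points at marker shifts of 0.5 to 1.0 SD. Interaction estimates will be imprecise at 22 per group (step 7), which favours reporting intervals over relying on a test.

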### **9.4 Interim analysis**

Not applicable

## **10. ETHICAL CONSIDERATIONS**

### **10.1 Regulation statement**

The study will be conducted according to the principles of the Declaration of Helsinki (version 9 October 2004) and in accordance with the Medical Research Involving Human Subjects Act (WMO).

### **10.2 Recruitment and consent**

Patients will be shortly informed about the outline of the study by their physician-in-charge, and asked if they are willing to receive further information. Subsequently, the local investigator or research nurse will provide detailed verbal and written information about the study. The patients will be given at least two weeks to consider participation. Participation is only possible after giving written informed consent, which will be asked by the local investigator.

### **10.3 Objection by minors or incapacitated subjects**

Not applicable

### **10.4 Benefits and risks assessment, group relatedness**

The potential value of this study lies in gaining insight in the process of artery calcification in patients with ESRD. With conventional dialysis methods, progression of arterial calcification occurs alarmingly fast. On theoretical grounds, it is plausible that progression is attenuated in patients with a renal transplant (low/normal phosphate, normal/high calcium) and patients on nocturnal hemodialysis (normal phosphate, normal calcium). However, no long-term data are available on this subject. Therefore it is difficult to advise dialysis patients about registration at the Eurotransplant Kidney Waiting List, especially for patients with advanced age, who have substantial perioperative morbidity and mortality.

The risk and burden to the patient are formed in this study by:

- calcium score MSCT: as described above (7.3 Study procedures) multislice CT is a very short procedure giving a low radiation dose (0.4-1.2 mSv);
- coronary MSCT: as described above (7.3 Study procedures) a coronary CT is also a very short procedure with a low radiation dose (3-4 mSv) (NB for comparison: a diagnostic abdominal CT scan delivers a dose of about 7-10 mSv);
- pulse-wave velocity: non-invasive measurement without risk;
- minor extra blood loss combined with routine venipuncture.

### **10.5 Compensation for injury**

The investigators have a liability insurance which is in accordance with article 7, subsection 6 of the WMO.

An insurance for the patients will be taken out in accordance with the legal requirements in the Netherlands (Article 7 WMO and the Measure regarding Compulsory Insurance for

Clinical Research in Humans of 23th June 2003). This insurance provides cover for damage to research subjects through injury or death caused by the study. This insurance applies to the damage that will be the result of the study and become apparent during the study or within 4 years after the end of the study.

#### **10.6 Incentives**

Subjects who need to travel from home to hospital by own means of transport only for investigations needed for this study, will be compensated by a travel reimbursement (€ 0.25/km plus parking costs, a lunch reimbursement of € 10,-).

## **11 ADMINISTRATIVE ASPECTS, MONITORING AND PUBLICATION**

### **11.1 Handling and storage of data and documents**

Medical information about the patients and data collected for the study are confidential, and will be coded to an individual patient code. The data will only be available for the investigators and medical staff involved in the medical care of the patients.

### **11.2 Monitoring and quality assurance**

The conduct of the study will be monitored. For details we refer to our monitoring plan (see attachment).

### **11.3 Amendments**

Amendments are changes made to the research after a favorable opinion by the accredited METC has been given. All amendments will be notified to the METC that gave a favorable opinion.

### **11.4 Annual progress report**

The investigator will submit a summary of the progress of the trial to the accredited METC once a year. Information will be provided on the date of inclusion of the first subject, numbers of subjects included and numbers of subjects that have completed the trial, serious adverse events/ serious adverse reactions, other problems, and amendments.

### **11.5 End of study report**

The investigator will notify the accredited METC of the end of the study within a period of 8 weeks. The end of the study is defined as the last patient's last visit.

In case the study is ended prematurely, the investigator will notify the accredited METC, including the reasons for the premature termination. Within one year after the end of the study, the investigator will submit a final study report with the results of the study, including any publications/abstracts of the study, to the accredited METC.

### **11.6 Public disclosure and publication policy**

The results of the study will be published in peer reviewed, international medical (nephrology) journals. Possible sponsors will not have influence on the publication of the results, irrespective of their nature.

